## Abstract

**Background:**

Over the past twenty years, the post-cancer rehabilitation has been developed, usually in a hospital setting. Although this allows better care organization and improved security, it is perceived as stressful and restrictive by the “cancer survivor”. Therefore, the transfer of benefits to everyday life is more difficult, or even uncertain. Staying in a thermal resort seemed to offer a good compromise: the security and structure of centralized reception in a thermal resort for treatment and medical supervision, and accommodation in a hotel with full dietary board. It combines institutional quality and security with the freedom of real life and the dynamics of a group formed under innovative conditions. This rehabilitation procedure was tested with the program PACThe (Program of Accompanying women after breast Cancer treatment completion in Thermal resorts) which was evaluated at one year in a randomized controlled trial involving 251 patients [1] and at five years in another study [2]. The results shown a significative improvement in many areas such as quality of life, functional abilities and sleep. The aim of this study is therefore to confirm the benefits of the PACThe program at six months for breast cancer women in complete remission in real-life conditions.

**Methods:**

The project PACThe Real-Life conditions is an observational trial in which 400 breast cancer women in complete remission will be sent to a 3 week thermal “post-cancer rehabilitation” program. Primary objective is to assess the quality of life until 12 months. The outcome will be measured with the self-questionnaire SF-36 [3] at five timepoints (inclusion visit, end of thermal resort, 6 months post-cure, 12 months post-cure and 18 months post-cure). The duration of patient participation in the study will therefore be 18 months. The main analysis will consist of comparing the SF-36 global score at 6 months with the baseline.

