#### Primary objective and outcome measure

The primary objective is to confirm the improvement in the quality of life at 6 months following the implementation of a post-therapeutic support and rehabilitation program for women in complete remission from breast cancer in thermal resorts (PACThe program), in real-life conditions, regardless of their treatment or the interval between the end of treatment and the start of the program.

The primary outcomes is the change in SF-36 global score [3] between baseline and at 6 months.

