### Sample size

The main analysis consists in comparing the change in SF-36 global score at 6 months from baseline to the value obtained in the PACThe study control group (historical comparator). In the randomized PACThe study, the difference in SF-36 global score between the experimental and control groups was 2.2 points at baseline (*p* =.3), and 9.5 points at 6 months (effect size = 0.63, *p* <.001), with a difference between 6 months and baseline of 11.9 points in the experimental group, and 4.6 in the control group, and a standard deviation between 15 and 16.

To determine the number of subjects required, it is assumed that the variation between 6 months and inclusion in this study will be slightly lower than in the PACThe study: expected value of 10 points. It is also estimated that the variability of the scores obtained will be greater than that observed in the PACThe study. Thus, a sample size of 400 should allow us to show a reasonable effect size of 0.2 (alpha risk equal to 5% and 95% power, for a one-sample Student’s t-test), and compensate for an estimated 15–20% drop-out rate.

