### Statistical analysis

The main analysis consists of comparing the change in SF-36 global score [3] between 6 months and baseline with the value obtained in the PACThe control group (historical comparator) using a Student’s t-test (or a non-parametric test depending on the data distribution). All patients who will not respond to the questionnaires at 6 months will be excluded from the analysis.

The evolution of the SF-36 global score over time (repeated data) will be analysed using mixed-effects linear regression models, followed, in the event of a statistically significant result, by post-hoc pairwise comparisons at different time points, with correction for multiple comparisons).

Confidence interval estimates of observed effects (changes in measurements at different time points post-program vs. baseline) will be used for comparison with the effects observed in the PACThe study, as well as analysis in subgroups defined by age, menopausal status and type of anti-cancer treatment.

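### The abstract states the main analysis as 6 months against baseline and the objective as 12 months; the body tests the 6-month change against the PACThe control group, and the abstract should be brought into line

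*Protocol article*

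**What the plan says.** **Main analysis.** The abstract (Methods) says "The main analysis will consist of comparing the SF-36 global score at 6 months with the baseline". The Sample size section gives the main analysis as "comparing the change in SF-36 global score at 6 months from baseline to the value obtained in the PACThe study control group (historical comparator"). The Statistical analysis section agrees: the 6-month change is compared "with the value obtained in the PACThe control group (historical comparator) using a Student’s t-test", or by a non-parametric test if the distribution requires it. The Discussion also refers to a comparison with the control group of the earlier trial.

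**Time point.** The abstract (Methods) says "Primary objective is to assess the quality of life until 12 months". The abstract (Background) says "The aim of this study is therefore to confirm the benefits of the PACThe program at six months". The section Primary objective and outcome measure says "The primary objective is to confirm the improvement in the quality of life at 6 months" and defines the endpoint accordingly: "The primary outcomes is the change in SF-36 global score [3] between baseline and at 6 months". The section on secondary objectives lists the 12- and 18-month scores among the secondary endpoints.

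**Historical figures.** The Sample size section reports the earlier randomized trial "with a difference between 6 months and baseline of 11.9 points in the experimental group, and 4.6 in the control group", and a standard deviation of 15 to 16. It does not say whether that SD belongs to the scores or to the changes.

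**The concern.** This is a single-arm cohort, so the reference value is all that separates the effect of the programme from recovery that would have happened anyway. The document's own figures show such recovery: women in the PACThe control group gained 4.6 points in 6 months. A comparison with baseline credits that gain to the programme. A comparison with the control-group change does not.

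Both descriptions carry the label of main analysis, so they cannot be read as a primary and a secondary analysis. If both stay on record, a report that leads with a significant change from baseline could cite the abstract as its prespecification. The objective sentence adds a second inconsistency, because it names 12 months where the abstract's own Background and the body name 6.

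**Working it through.** **1. Reproduce the sample size.** Inputs from Sample size: effect size 0.2, alpha 5%, power 95%, one-sample t-test, drop-out 15–20%, total 400.

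- Two-sided, normal approximation: ((1.960 + 1.645)/0.2)² = 325 after rounding up. The exact noncentral t calculation gives 327.
- Inflated for drop-out: 327/0.85 = 385, 327/0.825 = 397, 327/0.80 = 409. The stated 400 lies in this range.
- One-sided: 272 evaluable, giving 320 to 340. This does not reproduce 400, so the calculation implies a two-sided test.

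**2. Does the sample size show which reference was meant?** The expected change is 10 points.

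- Against the control change: (10 − 4.6)/0.2 = 5.4/0.2, so SD = 27.
- Against zero: 10/0.2, so SD = 50.

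The section expects variability above that of the earlier trial but gives no figure. An effect size of 0.2 fits either reference, so the calculation alone does not decide. An SD of 50 would be more than three times the reported 15–16, which makes the control-group reference the likelier intention.

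**3. How the abstract's test behaves if the programme adds nothing.** Take the true mean change as 4.6 and the test as a two-sided 5% test of zero mean change. The number evaluable is 400 less 15–20%, that is 340 to 320. The SD of change is an assumption: 16 is the top of the reported range, 20 is an intermediate value, and 27 and 50 come from step 2.

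- Smallest significant mean change = 1.967 × SD/√n.
- Chance of rejection ≈ Φ(4.6 × √n/SD − 1.967). The table gives exact noncentral t values.
- Example, SD 27 and n = 320: 4.6 × 17.889/27 = 3.048; 3.048 − 1.967 = 1.081; Φ(1.081) = 0.860.

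| Assumed SD of change | Smallest significant change (n = 340 to 320) | Chance of rejecting zero when the true change is 4.6 (n = 320 to 340) |
|---|---|---|
| 16 | 1.71 to 1.76 | over 99.9% |
| 20 | 2.13 to 2.20 | 98.4% to 98.8% |
| 27 | 2.88 to 2.97 | 86% to 88% |
| 50 | 5.33 to 5.50 | 37.5% to 39.4% |

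If all 400 were evaluable, the SD 50 figure would rise to 45.1%.

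**4. The body's test in the same situation.** With 4.6 taken as a fixed constant, as the document does, the true change equals the null value and the test rejects about 5% of the time. At a true change of 10 with SD 27, its power is 94.6% (n = 320) to 95.7% (n = 340), in line with the stated 95%.

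**The case against.** The strongest reply is that the operative plan states one main analysis. Sample size and Statistical analysis agree on the comparison, the second names the test, and the Discussion points the same way. The departure is one sentence in an abstract. An abstract condenses, and comparing 6 months with baseline is how the change score is formed. On this view the error rates above describe a test that the analysis section does not plan.

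Much of this stands, and it rules out several stronger readings that a reader might infer.

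- *That a hypothesis of zero mean change is written into the plan.* It is not. The abstract gives no null, test or reference value. Zero is the natural reading of a comparison with baseline that names nothing else, but it remains an inference.
- *That the outcome definition in the body supports a zero null.* It does not. It defines the variable, which is the same change that the body then compares with the control group. An outcome definition need not name the comparator.
- *That the plan offers a 12-month primary test as an alternative.* It does not. Wherever a time point is given for the main analysis, the abstract included, it is 6 months. Only the objective sentence is wrong.
- *That the abstract's test would certainly call an ineffective programme a success.* It would probably do so at SDs of 16 to 27. At SD 50 the significance threshold rises above 4.6 and rejection falls below one half.
- *That the registry entry is wrong.* It is not at hand, so nothing can be said about it.

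The reply does not remove the conflict itself. Condensing can drop detail, but here what was dropped is the reference value, and in a single-arm study that changes the question being tested.

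**Conclusion.** The point holds as an inconsistency in the stated primary analysis and its time point, between the abstract and a body that is explicit and consistent. It does not show that the analysis planned in the body is unsound.

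Its size depends on the SD of change, which the document does not give. If the programme added nothing beyond the 4.6 points seen in the PACThe control group, the test that the abstract suggests would be significant about 86% to over 99% of the time for SDs of 27 down to 16, and about 38% to 39% of the time at SD 50, with 320 to 340 evaluable. The body's test would be significant about 5% of the time.

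These figures assume a two-sided 5% level, a zero null read into the abstract, and 4.6 as a known constant and as the true change without benefit. Even at the SD most favourable to the abstract, the rate is several times the nominal 5%, so the text should be settled before the data are analysed.

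**What to change.** State one primary analysis wherever the study is described: the mean change in SF-36 global score from baseline to 6 months, compared with the change in the PACThe control group (4.6 points in Sample size), two-sided at 5% as the sample size implies. Specifically:

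- In the abstract (Methods), replace the comparison with baseline by this comparison, and give the primary objective as 6 months.
- Label the plain change from baseline as descriptive.
- Keep 12 and 18 months as secondary, as the section on secondary objectives already has them.
- Check that the registry entry gives the same primary analysis and time point, and correct it only if it does not.

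The cost is a change of wording. The sample size, data collection and the test set out in the Statistical analysis section stay as they are.

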**Discussion:**

This study aims to investigate the improvements in quality of life of 3 weeks stay at thermal resort for breast cancer women in complete remission. The comprehensive overview of the program PACThe will likely contribute to enhancing thermal therapy post-cancer rehabilitation in this population in real life conditions.

**Trial registration:**

The PACThe Real-Life conditions trial is a prospective observational study registered at the ANSM registry (2022-A00171-42) on March 1, 2022. This study has been registered on ClinicalTrials.gov: NCT05433077. Protocol: version 4, 22 December 2022.

## Background and aims of the study

As a result of early detection methods and increasingly effective treatments, more and more patients are surviving breast cancer. For instance, according to the World Health Organization, in 2022, the 5-year survival rates for breast cancer in western Europe exceeded 90% [4]. Therefore, improving the quality of life after treatment is a major challenge for oncologists.

Breast cancer patients often experience a significant decline in their quality of life (QoL) after surgery, chemotherapy, and radiotherapy which can lead to depression symptoms in the months following treatment.

Physical capacity constitutes a fundamental component of overall QoL, but cancer treatments frequently reduce physical capabilities, often due to surgical complications and metabolic changes resulting from chemotherapy, causing weight gain. The NHANES study shows that a significant portion of survivors spend most of their day in sedentary or low-intensity activities, leading to higher body mass index (BMI) and decreased physical QoL [5]. Additionally, post-breast cancer physical activity has an impact on survival, with a meta-analysis showing a significant reduction in mortality [6], and has been linked to better overall health [7].

However, encouraging cancer survivors to engage in physical activity remains a difficult task due to significant exercise barriers, such as fatigue, that impede their participation and commitment to cancer rehabilitation programs [8]. This is why participation in a specific rehabilitation program had to be carefully considered.

Post-cancer rehabilitation has been developed over the last twenty years. Most programs are implemented in hospital settings, which ensure the best possible safety and organization of care, but are perceived as restrictive and stressful for the “cancer survivor” after long months of heavy treatment; in addition, the transfer of benefits to everyday life is more difficult, if not uncertain. Outpatient treatment is less prone to these drawbacks, but limits access to people living in sufficiently large urban areas.

Staying in a thermal resort seemed to offer a good compromise: the security and structure of centralized reception in a thermal establishment for treatment and medical supervision, and accommodation in a hotel with full dietary board. It combines institutional quality and security with the freedom of real life and the dynamics of a group formed under innovative conditions.

Traditionally, programs in thermal resorts have been contraindicated for cancer patients during progression. However, during periods of complete remission, thermal programs can be a beneficial complementary therapy [9].

The “PACThe” program (Program of Accompanying women after breast Cancer treatment completion in Thermal resorts) enabled women treated for breast cancer (severe forms having received chemotherapy, surgery, radiotherapy) and in complete remission to be cared for in thermal establishments on a full-board dietary basis. The objectives of the program were to improve the patients’ quality of life by restoring their functional capacities, ensuring efficient weight control, combating stress and compensating for social and socio-aesthetic handicaps. To this end, the program combined hydrothermal balneotherapy, adapted physical activity, nutritional and dietary education, socio-aesthetic advice and psychological follow-up.

The program’s impact was evaluated at one year in a randomized controlled trial involving 251 patients (number calculated according to the assigned objective of improvement in the primary endpoint) [1]. This trial was complemented by an ancillary medico-economic study that was published separately [10]. A third study assessed quality of life (the study’s primary endpoint) at five years in surviving patients [2].

The results at one year show that implementation of the program is statistically significantly associated with an improvement in the following elements: quality of life measured with the SF36 QoL scores [3] at 6 and 12 months and compared between the “SPA group” and the “control group”; functional capabilities; weight control, particularly in overweight patients; depressive situation; sleep; level of physical activity in previously active patients; and return to work [1].

The intervention proved to be cost-effective at one year for all program participants and at six months for women who had returned to work. The main difference was in the use of physiotherapy, which was higher for patients in the control group [10].

At five years, the significant difference in quality of life was maintained between the two groups (*p* =.009 with a delta of 7.2 in the SF36 QoL score [3]), while mortality rates did not differ.

On the strength of all these results, the post-breast cancer rehabilitation program carried out as part of a stay at a thermal resort and implementing the program evaluated by the PACThe study has received financial support from the French health insurance scheme.

The study “PACThe program in real life” is a real-life trial to evaluate the post-breast cancer rehabilitation program PACThe. The thermal resort setting ensures the safety and availability of care, while remaining closer to real-life conditions than a stay in a healthcare facility.

The direct benefit for patients is a potential improvement in quality of life, the aim of the study being to show a lasting improvement in quality of life following the proposed program. At first sight, there are no foreseeable risks for patients.

The primary aim of the study is to validate that the beneficial results on the quality-of-life score (SF36) of the PACThe study so it could be extended to all women in post breast cancer (medically attested complete remission) regardless of their treatment or the time between the end of their treatment and the start of their thermal program.

Secondary aims are to study the effectiveness of the PACThe program in real life, according to subgroups, and to compare the effects observed (at different time points) with those observed in the PACThe study at the same time points.

## Design and methods

### Design

The study design is a longitudinal cohort observational study within an approved post-therapeutic support and rehabilitation program.

### Objectives and outcomes

All outcome measures will be assessed at baseline and at 6 months (i.e., after concluding the intervention period).

#### Primary objective and outcome measure

The primary objective is to confirm the improvement in the quality of life at 6 months following the implementation of a post-therapeutic support and rehabilitation program for women in complete remission from breast cancer in thermal resorts (PACThe program), in real-life conditions, regardless of their treatment or the interval between the end of treatment and the start of the program.

The primary outcomes is the change in SF-36 global score [3] between baseline and at 6 months.

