### Setting and eligibility criteria

Participants have been recruited through referral from French physicians prescribing thermal treatments (among participating centers). The thermal resorts also promote the program in their brochures and on their websites, so that patients and doctors are aware of it. Eligible participants are women aged 18 to 75 who have undergone breast cancer treatments such as chemo- and/or radiotherapy, in the absence of residual or progressive disease, and whose treatment has been completed (with the exception of hormone therapy). The exclusion criteria are defined as follows:

Progressive or metastatic cancer.Patient suffering from disability.Severe personality or eating disorders (craving, bulimia, etc.)Underweight (BMI < 18.5 kg.m-2) or severe to massive obesity (BMI > 35 kg.m-2).Refusal to participate.Contraindication to physical activity (whether cardiovascular or related to musculoskeletal pathology); lymphedema is not a contraindication.Participation in another clinical study.Insufficient knowledge or understanding of the French language to correctly complete a quality-of-life self-questionnaire or to answer a dietary questionnaire.The medical contraindications to thermal treatment validated by the Société Française d’Hydrologie et de Climatologie will be applied and are as follows:Severe alterations in general condition (progressive infectious conditions, renal or hepatic insufficiency, cirrhosis, respiratory insufficiency, etc.)Severe or acute hemorrhagic rectocolitis and Crohn’s disease.Severe immunodeficiencies.Recent phlebitis.Hypertension.

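### The primary test holds a cohort enrolled regardless of treatment or interval to a fixed 4.6-point benchmark from PACThe controls with severe, chemotherapy-treated disease, so programme effect and population difference cannot be separated

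*Protocol article*

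**What the plan says.** - **Test.** The Statistical analysis section compares the 6-month change from baseline "with the value obtained in the PACThe control group (historical comparator") by Student's t-test, or a non-parametric test. The Sample size section plans for a one-sample t-test. No covariate, weighting, matching or restriction is attached to this test.
- **Benchmark.** The Sample size section gives PACThe changes of "11.9 points in the experimental group, and 4.6 in the control group".
- **Where the benchmark comes from.** The Background describes the PACThe women as "severe forms having received chemotherapy, surgery, radiotherapy", in complete remission.
- **Who is enrolled now.** Eligible are "women aged 18 to 75 who have undergone breast cancer treatments such as chemo- and/or radiotherapy", with treatment completed apart from hormone therapy. No limit on time since treatment is set. The primary objective is framed as holding "regardless of their treatment or the interval between the end of treatment and the start of the program".
- **Related analyses.** The Statistical analysis section also plans confidence intervals for changes from baseline, to be set against the PACThe effects, and subgroups by age, menopausal status and type of anti-cancer treatment.
- **Data.** Treatments received and surgery are recorded at inclusion (Intervention and participant timeline). Time since end of treatment is not among the items listed there or under Data management and monitoring.

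**The concern.** A one-sample test against a constant attributes to the programme everything by which the cohort's change exceeds that constant. This is right only if 4.6 points is what these women would have gained without the programme. The figure was observed in a narrower group, and the study widens precisely the features (treatment received, time since treatment) that could plausibly alter spontaneous recovery. The Sample size section adapts two planning values to the new setting: it lowers the expected change and raises the expected variability. It leaves the comparator as it was.

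At stake is the study's main claim. The Discussion says that the PACThe effects are to be validated by comparison with the PACThe control group, and the Background says that the result is to be extended to all women in remission. A benchmark error would feed directly into both.

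**Working it through.** **Inputs**
- From the Sample size section: control change 4.6; "expected value of 10 points" for this cohort; "a sample size of 400 should allow us to show a reasonable effect size of 0.2"; alpha 5%, power 95%, drop-out 15–20%; and, for PACThe, "a standard deviation between 15 and 16".
- Evaluable women: 400 × 0.80 = 320 to 400 × 0.85 = 340. I use 330 as the mid-value.

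**1. The plan's own figure.** A two-sided one-sample t-test with d = 0.2 and 95% power needs 327 evaluable women (noncentral t). Inflated for drop-out, that is 327/0.85 = 385 and 327/0.80 = 409, which bracket 400. The stated sample size reproduces, so the issue is bias and not arithmetic.

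**2. The benchmark is internally consistent.** 11.9 − 4.6 = 7.3, and the between-group differences quoted for 6 months and baseline give 9.5 − 2.2 = 7.3.

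**3. Implied SD.** The planned excess is 10 − 4.6 = 5.4 points. With d = 0.2, SD = 5.4/0.2 = 27. The PACThe value of 15–16 may be the SD of scores rather than of change, since 9.5/0.63 = 15.1 recovers it from the 6-month difference. The documents give no SD labelled as that of change.

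**4. Bias.** Let e be the true programme effect and b the amount by which this cohort's untreated change exceeds 4.6. The expected contrast is (4.6 + b + e) − 4.6 = e + b. The error is b, point for point, at any n.

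**5. Consequence if b is positive (assumed b = 2.4, e = 0, n = 330).** P(significant in favour) ≈ Φ(b/SE − 1.96), with SE = SD/√330.

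| SD | SE | b/SE − 1.96 | Probability |
|---|---|---|---|
| 27 | 1.486 | −0.345 | 0.365 |
| 20 | 1.101 | 0.220 | 0.587 |

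The nominal value is 0.025. The exact noncentral t gives 0.363 and 0.585. For other assumed errors at SD 27 and 320–340 evaluable women, the probability is about 10% at b = 1, 26–27% at b = 2 and 51–53% at b = 3.

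**6. Consequence if b is negative (assumed b = −2).** A true excess of 5.4 appears as 5.4 − 2 = 3.4. At SD 27, power falls from about 95% to 61–64%.

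**7. Reversal point.** The test favours the programme exactly when the lower 95% confidence limit of the mean change lies above the benchmark. That limit is therefore the benchmark at which the conclusion reverses. If the planning values came true (mean change 10, SD 27, n = 330), it would be 10 − 1.967 × 1.486 = 7.1, so the conclusion would survive a benchmark error of up to 7.1 − 4.6 = 2.5 points.

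**The case against.** The strongest reply is that this is an openly declared observational cohort with a historical comparator, that non-comparability comes with such a design, and that the wider population is the intended target. That stands, and no concurrent control arm is being asked for. Supporting analyses may also sit in an analysis plan that is not shown. But the primary test is stated in the article, and as stated it cannot distinguish the two sources of change.

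The plan is not blind to treatment heterogeneity. The treatment-type subgroups and the confidence-interval comparison with PACThe are real mitigation, and the lower limit in step 7 would come out of the intervals already planned. What they lack is a named subset matching the PACThe profile, a comparison of that subset with 4.6, and any link to the primary conclusion.

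Four stronger readings are tempting and are not supported:
- **That the result will be inflated.** The sign of the difference is unknown. If women further from treatment recover less spontaneously, 4.6 is a demanding benchmark and the effect is understated.
- **That false positives would reach about 80%.** This follows from the same 2.4-point error at SD 15.5, but the plan expects more variability than PACThe showed, and its figures imply 27.
- **That covariate adjustment or weighting against PACThe controls is the necessary remedy.** The documents do not show that patient-level PACThe data are available. On the Background's description, treatment would not vary among those controls. Time since treatment is not a listed item.
- **That PACThe is known to have limited time since treatment.** The article does not say so. It only presents disregard of the interval as an extension.

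Finally, the Abstract's Methods paragraph describes the main analysis as 6 months against baseline. On that version the benchmark disappears, but so does any allowance for natural recovery, so it does not answer the point.

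**Conclusion.** The point holds as a limit on interpretation. The test in the Statistical analysis and Sample size sections cannot tell a programme effect from a difference in untreated recovery between this cohort and the PACThe controls, and the existing subgroup plans address this only partly. The bias equals the benchmark error, with sign and size not derivable from the documents. The 36% (SD 27) and 59% (SD 20) rest on an assumed 2.4-point error, no programme effect, 330 evaluable women and a two-sided 5% test. They show how sensitive the test is and do not predict the result. The study remains useful. What changes is how far its primary result can be read as a programme effect in the wider population.

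**What to change.** In the Statistical analysis section:
1. Pre-specify, as a key supporting analysis, the same comparison with 4.6 restricted to women who had chemotherapy, surgery and radiotherapy.
2. Report beside the primary result the benchmark at which its conclusion reverses, that is, the lower confidence limit of the mean change.
3. State that the claim of a programme effect over untreated recovery applies to the PACThe-profile subset. The wider-cohort result is to be described as an uncontrolled change from baseline unless the restricted analysis also has its lower confidence limit above 4.6. Even then, the wider claim assumes that 4.6 carries over, and item 2 shows how much error it tolerates.

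**Cost.** Text and analysis time; no extra patients and no new data items. The restricted analysis is less precise. If half of 330 women had the PACThe profile (an assumption; the share is not given), SE = 27/√165 = 2.10, and power for a 5.4-point excess would be about 72%. It should therefore stay a supporting analysis.

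Adjustment or weighting against PACThe controls is optional, only if patient-level PACThe data can be obtained. It cannot include time since treatment unless that item is recorded.
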